**Fig. 2 Fig2:**
[figure not shown]
CONSULT SWAT schema. * CRF, Case Report Form. Return of CRF indicates consent to participate

### Outcomes

The primary outcome is the quality of proxy consent decision as measured by the Combined Scale for Proxy Informed Consent Decisions (CONCORD) scale, which is a novel outcome measurement instrument [48]. The CONCORD scale was developed following a consensus study which identified the core outcomes that should be measured when evaluating interventions to enhance proxy decisions and a scoping review which found a lack of appropriate outcome measurement instruments [49]. It has previously undergone feasibility and acceptability testing in a hypothetical decision-making situation [48] and will be concurrently validated during the SWAT. CONCORD scores will be recorded both for consultees and legal representatives who do provide agreement to participation on the person’s behalf and those who decline participation. The timing of outcome measure completion will be aligned with the host trial processes but it is expected to be completed in a relatively short timeframe following the decision.

Secondary outcomes include selected CONCORD subscales of values clarity and preparedness, and where possible the proportion of consultees and legal representatives who provide agreement to participate on the person’s behalf and the proportion who decline participation and subsequent retention in the host trials.

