**Discussion:**

This SWAT will generate the first evidence for recruitment interventions for trials involving adults lacking capacity to consent and add to knowledge about the use of decision support interventions in trial participation decisions. The SWAT will be embedded in a range of trials, and the heterogenous nature of the host trials, settings and populations involved will enable the intervention to be evaluated in a wide range of contexts. However, a pragmatic and flexible approach to conducting the SWAT is needed.

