**Consent process**	
Researchers stressed the need to reduce the informational and consent burden for SWAT participants by avoiding a ‘double consent process’. Requiring an extra layer of consent for the SWAT might deter people from participating in the SWAT and acting as a consultee/legal representative host trial. Given the low-risk nature of the study and the impracticability of gaining consent prospectively prior to randomisation or receiving the intervention, consent to providing data was considered appropriate. This could be achieved through the return of the questionnaire indicating consent to participate. Researchers stressed the importance of harmonising information provided to family members about the host trial and SWAT in order to create a ‘whole package’ and improve clarity.	

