### Recruitment

SWAT participants will be identified in accordance with the host trial recruitment processes and their arrangements for recruiting people who lack capacity to consent. Recruitment processes are likely to differ between host trials and may differ between participating sites. As part of aligning the SWAT with the host trial processes, the procedures for identifying eligible participants for the SWAT will be discussed and agreed in advance for each host trial and participating site. The SWAT will use a proportionate approach to informed consent in accordance with HRA guidance [46]. Brief information about the SWAT will be provided to family members approached to act as a consultee or legal representative through a combined information sheet and questionnaire. The information sheet will include the purpose of the SWAT and data protection arrangements, and that completion and return of the questionnaire indicates consent to participate in the SWAT. SWAT participants can also provide their contact details if they are willing to be contacted to take part in an interview for the feasibility stage or process evaluation. SWAT participants and research staff delivering the DA intervention will be purposive sampled to ensure that a range of perspectives are included in the interviews. SWAT participants and research staff agreeing to take part in an interview will provide consent prior to commencing the interview.

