### Data collection

Following receiving the intervention (or standard information alone), SWAT participants will be asked to complete a questionnaire which includes questions relating to demographic data, use and views about the information received, decision outcome (agreeing to participation on the person’s behalf or declining) and the CONCORD scale. The questionnaire will be available in hard copy and online format depending on the host trial processes and will include an option to indicate if the participant is willing to be contacted about taking part in an interview. Where feasible, linked pseudonymised data will be collected on the recruitment and retention of the host trial participant. However, there are likely to be challenges around collecting and sharing this information which we have reported elsewhere [37]. A web-based system (Qualtrics) will be used to enter data online, either directly or from completed paper questionnaires. Interviews will also be conducted remotely with SWAT participants and research staff in both the feasibility stage and process evaluation. Interviews will be semi-structured using topic guides that have been informed by previous qualitative research [23]. Interviews will be audio-recorded and transcribed verbatim and pseudonymised prior to analysis. Data obtained during the interviews will be kept confidential. Voice data will be deleted at the end of the study and anonymised transcripts will be archived in line with Cardiff University policy. Quotes from the interviews may be used in the presentation of results but participants from either the SWAT or host trials will not be identifiable. Anonymised data may be shared with other researchers following the Centre for Trials Research processes for data sharing to ensure confidentiality, regulatory and ethical approvals.

Additional resource use data will be collected and assessed in each host trial using a method that corresponds with the host trial processes for approaching and informing potential consultees and legal representatives. For example, where recruitment is conducted face-to-face or during a consultation, the time required for the consultation and discussion will be recorded where possible.

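### Agreement, decline and host-trial retention have no stated denominator, and their only assured source is a form returned after allocation, so the arm comparison can be biased in a way the planned response-rate trigger would miss

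*Protocol article*

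**What the plan says.** The Outcomes section of the protocol article names three secondary outcomes besides the CONCORD subscales: the proportion of consultees and legal representatives who agree, "the proportion who decline participation and subsequent retention in the host trials". They are to be measured where possible, and no denominator is given.

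Data collection gives two sources:
- The decision is an item on the SWAT questionnaire, which covers "decision outcome (agreeing to participation on the person’s behalf or declining) and the CONCORD scale".
- Host-trial records are conditional: "Where feasible, linked pseudonymised data will be collected on the recruitment and retention of the host trial participant". The same section warns that "there are likely to be challenges around collecting and sharing this information".

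Under Recruitment, "completion and return of the questionnaire indicates consent to participate in the SWAT". The Fig. 2 caption says the same of the CRF. Table 1 (Consent process) gives the reason: "the impracticability of gaining consent prospectively prior to randomisation or receiving the intervention, consent to providing data was considered appropriate". Entry to the SWAT data therefore comes after allocation.

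The Analysis section bases its primary, intention-to-treat analysis on people who return questionnaires. It promises sensitivity analyses for non-response, and modelling if response rates differ between arms. Recruitment logs are named there for the feasibility stage only.

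**The concern.** A proportion agreeing is a fair randomised comparison only if everyone allocated is in the denominator. Here the one source that every host trial will have is a form that a family may or may not send back after deciding. If agreers and decliners return it at different rates, and the gap between those rates differs by arm, the returners no longer represent the allocated groups. A family that never gives a decision has no category at all. Table 1 (Intervention delivery) shows this could happen, since some families are approached by post with no researcher contact.

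Retention is a second case of the same problem. It exists only for people whose proxy agreed. If the DA changes who enters, retention among recruits compares groups that randomisation did not form.

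The stake is the claim in the Abstract: "This SWAT will generate the first evidence for recruitment interventions for trials involving adults lacking capacity to consent". The primary outcome is decision quality, so these secondary outcomes are the ones that bear directly on recruitment.

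**Working it through.** The article gives no agreement, return or retention rate and no sample size, so there is no figure to reproduce. **All rates below are assumptions**, chosen to show direction and range. For simplicity, every family either agrees or does not, and those who do not are called decliners.

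**Agreement among returners.** Let p be true agreement among all allocated, and ra and rd the return rates of agreers and decliners.

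- Overall return = p·ra + (1−p)·rd
- Observed agreement = p·ra / [p·ra + (1−p)·rd]
- Observed odds ratio = true odds ratio × (ra/rd in DA) / (ra/rd in control)

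Take p = 0.50 with the DA and 0.40 in control, a true difference of +10 points. The true odds ratio is (0.50/0.50)/(0.40/0.60) = 1.5. The sign reverses when the ratio of return ratios falls below 1/1.5 = 0.667.

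*Range.* Control: ra = 0.8, rd = 0.4, so observed agreement is 0.32/0.56 = 57.1%. DA: ra = 0.8, with rd varied.

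| DA rd | DA overall return | DA observed agreement | Difference from control |
|---|---|---|---|
| 0.4 | 60% | 0.40/0.60 = 66.7% | +9.5 points |
| 0.5 | 65% | 0.40/0.65 = 61.5% | +4.4 points |
| 0.6 | 70% | 0.40/0.70 = 57.1% | 0.0 points |
| 0.7 | 75% | 0.40/0.75 = 53.3% | −3.8 points |

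The first row has the same return pattern in both arms, and the distortion is slight. If agreers and decliners return equally often within each arm (0.8 throughout), the difference is exactly +10. In all four rows overall return differs from the control arm's 56%, so a difference in response rates would be there to see.

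*Equal overall return.* Control as before (0.80/0.40). DA: ra = 0.60, rd = 0.52.

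- Control return: 0.40×0.80 + 0.60×0.40 = 0.56. Observed agreement: 0.32/0.56 = 57.1%.
- DA return: 0.50×0.60 + 0.50×0.52 = 0.56. Observed agreement: 0.30/0.56 = 53.6%.

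The true +10 points appears as −3.6, with identical 56% response in both arms. The ratio of return ratios is (0.60/0.52)/(0.80/0.40) = 0.577, below 0.667.

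**Retention.** Retained per person allocated = p × retention among recruits. With the same p, and assumed retention among recruits of 80% (DA) and 90% (control):

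- Among recruits: 80% v 90%, a difference of −10 points.
- Per person allocated: 0.50×0.80 = 40% v 0.40×0.90 = 36%, a difference of +4 points.

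With control at 90%, the two contrasts have opposite signs whenever DA retention among recruits lies between 0.36/0.50 = 72% and 90%.

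**The case against.** The strongest reply has four parts.

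1. *The denominator is not stated, so it is not stated wrongly.* The sentence on returners concerns the primary analysis, and the SAP or full protocol may define these proportions. This stands: a returner denominator is an inference from consent by return and the questionnaire item. But a definition written later cannot supply counts that were never collected, and the article names no main-stage source for them.

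2. *A second source exists.* Linked host-trial data are planned, and the article is open about their limits. This also stands, so it would be wrong to say the questionnaire is the only source. It is the only assured one, and nothing says linkage reaches families who did not return the form.

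3. *Non-response is already addressed.* The sensitivity analyses and conditional modelling reduce the problem. The modelling trigger, however, is a difference in response rate, and the equal-return case shows bias without one.

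4. *Retention ordinarily describes people who joined.* This is fair. Retention per person allocated answers a different question, so it belongs beside the usual figure and should not replace it.

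A reader might also infer that decliners are known to return less often, or that the recruitment effect will come out reversed. The article supports neither. It gives no return rates, and it plans to record CONCORD scores from those who decline as well.

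**Conclusion.** The concern holds in a limited form. As described, the agreement and decline comparison rests on a source that is selected after allocation, and the planned modelling trigger would not detect every harmful selection. Under the assumed rates a true +10 points appears as anything from +9.5 to −3.8, and as −3.6 at equal overall response.

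Material bias needs return to depend on the decision and that dependence to differ by arm. The article gives no evidence on either, so the likely size cannot be estimated. Where the return pattern is the same in both arms, the distortion is small.

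The retention arithmetic shows a change of sign in the retention contrast. It should not be read as reversing the recruitment effect; that possibility comes only from selective return. These are secondary outcomes, so this is a change that should be made, not one on which the SWAT stands or falls.

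**What to change.** Before recruitment opens in each host trial, agree to obtain aggregate, non-identifying counts by SWAT arm from its recruitment or screening log: family members allocated (or approached), agreed, declined, no response, and retained. This extends to the main SWAT the logs that the Analysis section names for the feasibility stage, and it does not depend on individual linkage.

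Then:
- Use all family members allocated as the denominator for agreement and decline, with no response as its own category.
- Report retention per person allocated beside retention among recruits, and label the latter descriptive.
- Where a host trial cannot supply the counts, label its questionnaire-based proportions descriptive.

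The cost is one small count table per host trial and a few lines of definition. Some host trials may be unable to provide the table, which is why it should be settled in advance.

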### Data collection

Following receiving the intervention (or standard information alone), SWAT participants will be asked to complete a questionnaire which includes questions relating to demographic data, use and views about the information received, decision outcome (agreeing to participation on the person’s behalf or declining) and the CONCORD scale. The questionnaire will be available in hard copy and online format depending on the host trial processes and will include an option to indicate if the participant is willing to be contacted about taking part in an interview. Where feasible, linked pseudonymised data will be collected on the recruitment and retention of the host trial participant. However, there are likely to be challenges around collecting and sharing this information which we have reported elsewhere [37]. A web-based system (Qualtrics) will be used to enter data online, either directly or from completed paper questionnaires. Interviews will also be conducted remotely with SWAT participants and research staff in both the feasibility stage and process evaluation. Interviews will be semi-structured using topic guides that have been informed by previous qualitative research [23]. Interviews will be audio-recorded and transcribed verbatim and pseudonymised prior to analysis. Data obtained during the interviews will be kept confidential. Voice data will be deleted at the end of the study and anonymised transcripts will be archived in line with Cardiff University policy. Quotes from the interviews may be used in the presentation of results but participants from either the SWAT or host trials will not be identifiable. Anonymised data may be shared with other researchers following the Centre for Trials Research processes for data sharing to ensure confidentiality, regulatory and ethical approvals.

Additional resource use data will be collected and assessed in each host trial using a method that corresponds with the host trial processes for approaching and informing potential consultees and legal representatives. For example, where recruitment is conducted face-to-face or during a consultation, the time required for the consultation and discussion will be recorded where possible.

All quantitative and qualitative data will be stored securely and in compliance with the Data Protection Act 2018 and with the Centre for Trials Research Data Protection and Participant Confidentiality Standard Operating Procedures (SOPs). A Data Management Plan will be in place detailing the management of data for the study.

### Analysis

During the initial feasibility stage, acceptability and feasibility will be assessed through recruitment rates to the SWAT via recruitment logs and CRF return, evaluating completeness of data items, and qualitatively through interviews with family members and research staff (recruiters and members of the trial co-ordination team) including uptake of the invitation to take part in an interview. Provided no changes are required that materially changes the SWAT components, data from the feasibility stage will be subsequently included in the meta-analysis.

In the main SWAT, statistical analysis will be performed using statistical software (Stata). Descriptive statistics will report participant demographic data across the two arms of the SWAT. A two-stage meta-analysis strategy will be used to analyse each individual SWAT taking into account whether it was individually randomised, or cluster randomised to generate trial-level summary statistics, with the results from each individual SWAT then combined across trials. Primary analysis will be on an intention-to-treat basis based on those who return questionnaires. Sensitivity analyses will be undertaken to assess the robustness of the results to non-response to questionnaires, and modelling undertaken if there is a differential response rate between those who receive the decision aid and those who do not.

Where additional data has been collected on recruitment and retention of host trial participants, subgroup analyses will investigate differences between decision outcomes, i.e. whether or not the consultee/legal representative’s decision was that the person should participate in the host trial. Further subgroup analyses and sensitivity analyses may investigate differences between host trial results based on factors such as underlying recruitment rates of the host trials, and timing to outcome measure completion.

Qualitative analyses will be supported by data analysis software (NVivo). At the feasibility stage, interview data will be analysed thematically to provide an understanding of participants’ views about the acceptability of the SWAT, intervention, and outcomes. During the process evaluation, qualitative data from the interviews will be analysed using framework analysis and integrated with the quantitative data to contribute to the assessment of fidelity and other implementation factors. Attention will also be paid to any adaptations that were made in different contexts in order to implement the intervention (which may also undermine intervention fidelity), any contamination between arms or unblinding events, and any changes over time. A key focus of the analysis will be to further develop and test the logic model underlying the decision support intervention to examine the likely mechanisms of action, and the active components.

The contextual factors that may be associated with variation in outcomes will be explored in order to analyse how implementation may vary from one context (host trial, population, setting etc) to another, and whether the intervention has different effects in different contexts even if its implementation does not vary [34]. Contextual moderators will be analysed through detailed description of the nature of the host trial, trial population and consultee/legal representative population, setting, and trial processes that are recorded by the research team through discussion with the host trial team. Qualitative interview data will also be analysed to explore the use and implementation of the decision aid in a range of different contexts.

As part of the concurrent validity testing of the CONCORD scale, factor analysis will be conducted to identify items that most clearly represent the content domain of the underlying construct and any redundancy through testing the internal consistency. Supported by qualitative data from the feasibility stage and process evaluation, this will enable further exploration of existing hypotheses about relationships between constructs and items, and ongoing revision of the underlying theory and construct validation.

The cost-consequence analysis will analyse quantitative resource use data such as the time required for training on the intervention, costs associated with delivering the intervention (e.g. printing, postage), and time required to deliver the intervention, in addition to the usual costs associated with delivering standard trial information. The costs will then be tabulated from the NHS and societal perspectives and presented alongside the CONCORD measure and relevant contextual information using a descriptive table [35].

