### Intervention and allocation

The intervention consists of the DA (a 12-page A5 colour booklet ‘Making decisions about research for others’) which is provided to family members in addition to standard study information about the host trial. The control is standard study information alone for family members. The DA is intended to be used by the family member at the time they are making a decision about whether the person they represent should participate or not. The development of the DA and its contents are described elsewhere [30]. Briefly, it contains an explanation about why they are being approached, why adults lacking capacity are included in research, and a six-step guide to making a decision. It also includes a values clarification exercise to help them to understand what the advantages and disadvantages might be, and to consider how the person they represent would view them and come to a decision about participating or not. The DA is intended to be generic rather than host trial specific; however, the values clarification exercise and other sections help to identify features that are relevant to that particular decision context. The family member is encouraged to identify any areas they feel that they need more information in order to make a decision and to write down any questions they may have in the spaces provided. Depending on the method of communicating with consultees and legal representatives used in the host trial, the DA may be posted out to the participant to be read and completed remotely, or they may be provided with it (in person or remotely) ahead of a consultation with the recruiter (in person or via telephone or video conference) to discuss the participation of the person they represent in the host trial.

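### The planned subgroup split by the proxy's decision to agree or decline uses a post-allocation outcome, so arm comparisons within those groups are not randomised and are open to bias

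*Protocol article*

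**What the plan says.** All references are to the protocol article.

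- **Analysis.** The analysis is conditional: "Where additional data has been collected on recruitment and retention of host trial participants", then "subgroup analyses will investigate differences between decision outcomes". The sentence goes on to define these outcomes as whether or not the proxy decided that the person should take part in the host trial. It does not name the outcome to be compared, and nothing marks the analysis as descriptive or gives a method for groups formed after randomisation.
- **Intervention and allocation.** "The DA is intended to be used by the family member at the time they are making a decision".
- **Data collection.** "Following receiving the intervention (or standard information alone), SWAT participants will be asked to complete a questionnaire". That questionnaire holds both the decision and the CONCORD scale.
- **Outcomes.** "The primary outcome is the quality of proxy consent decision as measured by" CONCORD, which is scored for agreers and decliners alike. The secondary outcomes include "where possible the proportion of consultees and legal representatives who provide agreement to participate" and the proportion who decline.
- **Analysis, next sentence.** Further subgroup and sensitivity analyses are optional. They may examine differences between host trial results by factors such as the host trials' underlying recruitment rates and "timing to outcome measure completion".

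**The concern.** A treatment-effect subgroup needs a factor that allocation cannot change. Randomisation then balances the arms within each level of the factor. The proxy's decision is not such a factor: it follows allocation, and the plan itself treats it as an outcome.

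Suppose the DA moves some families from declining to agreeing. The agreers in the DA arm then include families who would have declined with standard information, and the decliners in the DA arm have lost them. If those families differ in decision quality for other reasons, such as burden or confidence, the arms differ within each group before any effect of the DA on CONCORD.

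The protocol's own reasoning makes both parts plausible. The Discussion describes the DA as an intervention to enhance recruitment. The Background says that the burden proxies experience leads many families to decline. A within-group difference could therefore be read as the DA improving or worsening decision quality when it reflects only who ended up in each group.

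**Working it through.** The protocol states no sample size, effect size or SD, so there is no figure of its own to reproduce. The check has two parts.

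**1. Order of events.** Allocation comes first, then the DA or standard information, then the decision, then the questionnaire that records the decision and CONCORD (Intervention and allocation; Data collection). The subgroup variable is therefore post-randomisation, and by the Outcomes section it is also a secondary outcome.

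**2. Possible size.** Every input here is an assumption. Let CONCORD, in SD units, have correlation r with a latent leaning to agree, both standard normal. A proxy agrees when the leaning passes an arm-specific threshold, so that a proportion P agrees. The DA has no effect on CONCORD. With z = Φ⁻¹(P) and φ the normal density:

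- mean CONCORD among agreers = r·φ(z)/P
- mean CONCORD among decliners = −r·φ(z)/(1−P)

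Control arm, P = 0.50: φ(0) = 0.3989, so the means are ±r × 0.7979.

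*Case A: r = 0.5, agreement 50% to 65%.* At P = 0.65, z = 0.385 and φ = 0.3704.
- Agreers: 0.5 × 0.3704/0.65 = 0.285 in the DA arm, against 0.399 in control. Difference **-0.114 SD**.
- Decliners: −0.5 × 0.3704/0.35 = −0.529, against −0.399. Difference **-0.130 SD**.
- Whole DA arm: 0.65 × 0.285 − 0.35 × 0.529 = 0 to rounding. The overall comparison stays unbiased.

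*Case B: r = 0.3, agreement 50% to 60%.* At P = 0.60, z = 0.253 and φ = 0.3863.
- Agreers: 0.3 × 0.3863/0.60 = 0.193, against 0.239. Difference **-0.046 SD**.
- Decliners: −0.3 × 0.3863/0.40 = −0.290, against −0.239. Difference **-0.050 SD**.

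If r = 0, or if P is the same in both arms, both differences are zero.

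**Second model.** A simulation of 2,000,000 families per scenario used a logistic model for the decision. An unmeasured trait U acted on the decision (coefficient c) and on CONCORD (coefficient 0.6, total SD 1).

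| DA log-odds ratio on decision | c | True DA effect (SD) | Agreement, control / DA | Overall | Agreers | Decliners |
|---|---|---|---|---|---|---|
| 0 | 1 | 0 | 0.502 / 0.500 | -0.002 | -0.002 | 0.000 |
| 0.5 | 0 | 0 | 0.500 / 0.623 | 0.001 | -0.001 | 0.003 |
| 0.5 | 1 | 0 | 0.499 / 0.602 | 0.000 | -0.049 | -0.052 |
| 1.0 | 2 | 0 | 0.500 / 0.647 | 0.000 | -0.106 | -0.113 |
| 0.5 | 1 | 0.30 | 0.500 / 0.601 | 0.301 | 0.250 | 0.251 |
| 1.0 | 2 | 0.30 | 0.500 / 0.648 | 0.302 | 0.198 | 0.186 |

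The two models agree. The bias appears only when both conditions hold, it is similar in the two groups, and the overall estimate is not distorted.

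**The case against.** **The sentence names no outcome.** It never says that CONCORD will be compared between arms within agreers and within decliners. The analysis is also tied to linked recruitment and retention data, which a CONCORD-by-decision analysis would not need, because the questionnaire holds both. The authors may have meant to compare decision rates between arms, or to describe agreers against decliners. This stands in part: the wording is ambiguous. But comparing agreement rates between arms is already a secondary outcome and is not a subgroup analysis, and a description should be labelled as one. Calling it a subgroup analysis and defining the groups by decision makes a split by decision the natural reading. On any reading the sentence needs rewording.

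**Bias is possible, not shown.** This stands. Listing agreement as a secondary outcome does not show that the authors expect it to change, and the DA is described as helping families decide either way. A reader might infer that the within-group estimates are certainly biased. The documents support only that they are open to bias, with size and direction unknown.

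**No false contrast between the groups.** A reader might infer that the split would make the DA seem to work only for agreers, or only for decliners. The calculations do not support that, because the distortion is nearly equal and of the same sign in both groups.

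**Timing of completion.** A reader might extend the point to "timing to outcome measure completion", since the DA could change how long a family takes. The text does not support this. It places timing among factors for differences between host trial results, makes the analysis optional and groups it with sensitivity analyses, and the Outcomes section aligns timing with each host trial's processes. It would become a problem only if individual completion time were used as an effect modifier.

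**Subgroup detail may sit in an unseen analysis plan.** It may, but the choice of decision as the subgroup variable is stated here.

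**Conclusion.** The point holds in limited form. The plan commits to subgroup analyses by a variable that follows allocation and is one of its own outcomes. On the natural reading, CONCORD comparisons between arms within agreers or within decliners are not protected by randomisation. They are open to bias if the DA shifts the decision and the decision shares causes with CONCORD.

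With correlation 0.3 to 0.5, agreement up 10 to 15 points from 50% and no true effect, the spurious difference is about -0.05 to -0.13 SD in both groups. In the second model a true effect of 0.30 SD falls to between 0.25 and 0.19 SD. None of these inputs comes from the documents.

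The analysis is secondary and depends on linked data that the Data collection section expects to be difficult to obtain. The primary CONCORD analysis is untouched. This deserves correction before results by decision are examined, but it does not threaten the trial's main conclusion.

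**What to change.** 1. Remove decision outcome as a treatment-effect subgroup. Analyse it by arm as the secondary outcome it already is.
2. If CONCORD is shown by arm and decision, present it as a descriptive table labelled non-randomised, without inference about the DA's effect in either group.
3. Limit effect-modification analyses to factors fixed before allocation that the protocol supports: setting, acute or long-term loss of capacity, consultee or legal representative role, and host-trial processes. Relationship to the person could be added only if it is confirmed to be collected; the article mentions only demographic data.
4. Keep timing to outcome completion as a between-host-trial comparison or sensitivity analysis, and state that it will not be used as a participant-level effect modifier.

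The cost is a change of wording, with no new data. The small downside is that there will be no inferential subgroup result by decision.
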